### Study Sites

To ensure a complete understanding of the problems and implementation strategies of varied community pharmacy work systems, we will partner with 3 pharmacy organizations. First, Advocate Health is the 10th largest not-for-profit, integrated health system in the United States, with 70 community pharmacies that are geographically dispersed throughout urban and rural Wisconsin and Illinois. Second, UW Health is the integrated health system of the University of Wisconsin–Madison, with 12 outpatient pharmacies. Third, Boscobel Pharmacy and Center Pharmacy are located in rural southwest Wisconsin and are independently owned.

Within each of these organizations, 2 pharmacies will participate that serve ethnically diverse populations and people in medically underserved areas that have high area deprivation indices based on income, education, employment, and housing quality for 6 pharmacy sites. In addition, all pharmacies will have at least read-only access to the electronic health records of their patients, which may serve as a tool to facilitate CCM.

We will also partner with Fitchburg Family Pharmacy to conduct in situ simulations, in which we will use simulated scenarios of patients with complex chronic health conditions in a pharmacy itself rather than in training facilities for the design and development phases (aim 2) of the project. Fitchburg Family Pharmacy is a medium-sized urban independent pharmacy that provides CCM to a diverse patient population.

### Project Aims

Table 1 describes our project structure, starting with problem analysis (aim 1) and continuing with design and development (aim 2), which will lead to implementation and evaluation (aim 3). An expert advisory board, comprising transdisciplinary stakeholders, will be formed to provide us with high-level consultation and content expertise for each of the 3 project aims. This board includes patients, caregivers, a pharmacy technician researcher, a pharmacy owner, primary care physicians, managers of independent, local, and chain pharmacies, and leaders of pharmacy and medical societies in Wisconsin.

**Table 1 table1:** Project structure guided by the Agency for Healthcare Research and Quality Request for Application 5-step methodology.

	Problem analysis (step 1)	Design (step 2) and development (step 3)	Implementation (step 4) and evaluation (step 5)
Aims	Identify and prioritize (aim 1)	Prototype and simulate (aim 2)	Pilot and evaluate (aim 3)
Methods	Observations and interviews Information flow diagraming Artifact analysis	Participatory design Simulation	Time motion Before and after evaluation Expert evaluation Surveys and interviews
Outputs	Resilience narratives Functional resilience analysis method diagrams	Prototypes Ideal interactions Detailed design specifications	Impact of prototypes on process and outcomes Tools to assess capacity for resilience Implementation guide

### Aim 1: Identify and Define Design Requirements

#### Overview

To develop effective and sustainable interventions, an in-depth problem analysis of the work system must be conducted. Thus, aim 1 seeks to understand and map work system resilience, including how WAI differs from WAD, how adjustments are created, and how outcomes are generated. Iterative data collection and analysis will allow continual refinement and clarification of the work system.

#### Observations

In-depth ethnographic observations will be conducted over 4 visits to each of the 6 pharmacy observation sites (Textbox 2). Study team members will debrief after each observation as well as in situ as needed to adjust observation approaches or focus on specific aspects of the workflow. We will complete 24 hours of observations over 4 days. Observed artifacts that reflect WAI, such as policies and procedures, memory aids, and cognitive tools, will also be collected and recorded. Full descriptive field notes will be produced immediately after each observational session. Data will be collected concurrently at each setting, and researchers will work across all settings so that comparisons between the settings can inform ongoing data collection strategies.

Observations at the pharmacy sites.
**High-level observation questions**
What contributes to variability in demand and capacity?What misalignment occurs between demand and capacity and why?What pressures, problems, or goals are pharmacists and technicians responding to when they create new ways to achieve outcomes?How and under what circumstances do adjustments or adaptations lead to successful and unsuccessful outcomes?
**Visit 1: exploratory evaluation**
Observe the pharmacy environment holisticallyIdentify staff roles and responsibilities, processes, procedures, flows of information and communication, coordinating mechanisms, and supporting tools and technologyIdentify interest areas for more precise and targeted observations in subsequent stages
**Visits 2 to 4: observations**
Observe the pharmacy staffIn-depth observations of important processes, such as shift-change handoffs and medication reconciliation for patients during hospital discharge, as processes critical to providing chronic care managementShort, structured discussions and facilitated reflection from staff on aspects of the concepts for applying resilience engineering model and using the systems engineering initiative for patient safety model components

#### Interviews

Semistructured interviews will be separately conducted with 2 pharmacists and 2 technicians from each of the 6 pharmacy locations to explore and follow up on issues from the previous observation stages to identify processes or areas for additional observation. Questions for the first round of interviews will focus on how people do their work and how they manage tricky situations, with probes about variability, adaptations, problems, and challenges (Multimedia Appendix 1). Questions for the second round will focus on staff experiences with, understanding of, and expectations for specific nondispensing services within community pharmacies (Multimedia Appendix 2). Interviews will be audio recorded and transcribed for analysis with participants’ consent.

#### Data Analysis

Data analysis will proceed in 3 stages. First, a combined deductive-inductive approach will be used to thematically analyze the observation and interview data. A coding scheme will be developed based on elements of the SEIPS model as well as important themes in the data not captured by the model (Table 2). Categories will be developed by constantly refining the coding scheme, and comparisons will be made between different respondents, different pharmacies, and different processes.

**Table 2 table2:** Aim 1 observation and interview coding scheme.

Levels	Comparison of WAD^a^ and WAI^b^
Teams of pharmacists and technicians	Interpersonal communication, including verbal and nonverbal Teamwork skills, including leadership and situation awareness
Technology	Usability, flexibility, adjustability, and adaptability
Internal environment	Interruptions and distractions Lighting Physical ergonomics of the workspace Crowding and disorganization
Tasks	Task demands and workload Contextual changes, including situation deviations from normal or expected Production pressure
Organization	Complexity, uncertainty, and risk Information flow, including quantity and pacing Culture and climate Policies and procedures Incentives and disincentives

^a^WAD: work as done.

^b^WAI: work as imagined.

Second, guided by the CARE model, we will expand on the SEIPS coding scheme to construct functional resilience analysis method (FRAM) models [36,40] to visualize WAD and articulate the discrepancies between WAI and WAD. FRAM models allow all activities within selected processes to be visualized to show how they relate to each other and how they interact, based on six aspects, namely (1) input, (2) output, (3) precondition, (4) resources, (5) time, and (6) control, demonstrating the system’s complexity [41]. Each process within the community pharmacy is linked, which allows the study of the variability of each process. That variability can produce amplified and unpredictable outcomes (either acceptable or unacceptable) [36,40].

Third, the themes generated by the deductive-inductive approach and the FRAM models will be used to create resilience narratives describing trajectories of activity linking misalignments of demand and capacity, adjustments, adaptations, and outcomes. The narratives will focus on how adjustments and adaptations (WAD) mediate between pressures caused by misalignments of demand and capacity and outcomes.

### Aim 2: Design and Develop MedSafeMap

#### Overview

Stakeholder-engaged participatory design and simulation-based research will be used in an iterative fashion to design and develop MedSafeMap, a package of components to optimize pharmacy staff interactions within their work system and with patients, and detailed pharmacy design recommendations. Standardized scenarios of patients with complex chronic health conditions will be developed to have both internal validity and fidelity to the real-world pharmacy environment. The goal is to create MedSafeMap components that will ultimately lead to pharmacy staff resilience and optimized patient interactions around CCM.

#### Participatory Design

Participatory design is an approach to system design that actively involves all stakeholders at several stages of the innovation process to help ensure that the result meets their needs and is usable [28]. Two stakeholder groups will be used: one group consisting of 5 community pharmacists and another group consisting of 5 technicians.

Stakeholder group meetings will be held 6 times, approximately every 6 to 8 weeks. The first 4 meetings will be held with the pharmacists and technicians separately because they have different work responsibilities, tasks, and concerns. We also want technicians to fully engage in MedSafeMap development without a pharmacist’s presence imposing a power differential. The resilience narratives and FRAM diagrams developed in aim 1, which demonstrate variability and resilience potential, will inform the design and development of the MedSafeMap. We will focus on the processes required to conduct CCM for patients with complex chronic health conditions, including the possibility of a communication tool to support a discussion of alternatives, enhanced instructions for patients, and cognitive aids to support memory. The final 2 meetings will involve MedSafeMap refinement. To do so, we will bring the pharmacist and technician groups together to work collaboratively. Textbox 3 provides a list of anticipated or possible MedSafeMap components. Completed MedSafeMap components will be peer reviewed by our advisory board to confirm that they will reproduce the experience in a real-world pharmacy. Scenarios will be piloted in the in situ simulated setting and refined before implementation in aim 3.

Current interactions and potential Medication Safety Map (MedSafeMap) components to encourage ideal interactions.
**Current interactions**
Chronic care management seen as important but has an impact on workload, which is a barrier to sustained services.Fragmented information across health care providersMedication information gap (eg, multiple pharmacies, no diagnoses, or laboratory values)Busy retail pharmacies lead to reduced interactions with patientsCoordination gap between pharmacists and caregivers, patients, and health care providersTechnicians limited by traditional rolesMedication concerns not adequately addressedLimited support and space for shared decision-making
**Potential MedSafeMap components**
Modeling behaviors: tactics to overcome communication barriers in pharmacies and engage health care providers; patient and family support to bridge the information gapInformation support: use technology or low-technology strategies to push eligible patients into the pharmacy workflow; create mechanisms that provide caregivers the opportunity to be involved before, during, and after an appointmentCognitive aids: physical structures to improve pharmacists’ and technicians’ situation awareness; supports in addressing high-priority medication needsCollaborative work support: facilitate a huddle between pharmacist and technician to create an appointment agenda, anticipate patient challenges, and review monitoring needsRole clarity and cross-training: empowering technicians as equal partners and leaders in the community pharmacy

#### Simulation-Based Research

In situ simulation [42], or simulation in an actual community pharmacy, will then be conducted to study the ergonomics and physicality of the work setting on performance. In situ simulations will also promote process and MedSafeMap refinement before deployment in actual pharmacies.

The final 2 stakeholder meetings will involve 3 rapid adaptive simulation cycles for MedSafeMap refinement (Figure 3). Each simulation cycle will include 5 different standardized patients (hired for the study). Each patient will represent 1 of the 5 different complex CCM scenarios that will include at least 2 chronic conditions and at least 1 social determinant of health (eg, a low health literacy patient with diabetes and congestive heart failure who is nonadherent to medications). Staffing and equipment, level of complexity, and other critical indicators identified in the participatory design will vary and allow for comparisons across the 5 patient scenarios. Creating robust and standard scenarios is important to mitigate threats to internal validity. Thus, we will devote considerable time to ensuring that MedSafeMap may be used in different patient cases and different community pharmacy settings (ie, is pharmacy agnostic; Figure 3).

**Figure 3 figure3:**

Simulation cycles.

In total, 10 pharmacist and technician dyads will be recruited to participate in each adaptive simulation cycle. In each adaptive cycle, the pharmacy and technician dyad will complete the simulation 5 times, once for each standardized patient. The process will be replicated for each of the 10 pharmacy dyads, resulting in 50 simulations per adaptive cycle. At the completion of each cycle, the study team will use the data collected, combined with significant reflection and formative evaluation, to refine MedSafeMap that facilitates resilience and encourages adaptation by pharmacy staff.

#### Data Collection

Four wide-angle video cameras will be used to record the simulation from locations that best capture how pharmacy staff interact with the physical space, communicate, share information, and use artifacts within the work system. In addition, 2 sets of eye-tracking glasses (Tobii Pro Glasses) [43-45], one each for the pharmacist and the technician, will be deployed to track eye movement in the natural world, which will inform the development of prototypes. Specifically, as pharmacy staff navigate the physical pharmacy space, the glasses collect data that will provide an understanding about which artifacts are most instrumental to performing CCM, factors that influence pharmacy staff and patient decision-making, and workflow. Gaze data will be recorded as pharmacy staff read and review information on prescriptions and prescription profiles in the pharmacy electronic health record and interact with and educate patients. Aim 2 will be accomplished in 3 steps, conceptualized in Table 3.

**Table 3 table3:** Aim 2 data collection procedures.

	Step 1	Step 2	Step 3
Tasks	Record simulations and document individual and collective behavior	Introduce MedSafeMap^a^ and record simulations: simulate with 10 pharmacist and technician dyads for each of 5 different standardized patients	Conduct individual debrief interviews with the pharmacists and technicians following completion of each simulated scenario
Goal	Identify patterns of interactions and thought processes	Reproduce situations identically to increase confidence in the MedSafeMap’s ability	Gain insights into the thoughts and cognitive processes of pharmacists and technicians
Output	Descriptive account of how community pharmacy staff make decisions or share information; understand rare events, such as sentinel medication errors	Explain variation in the outcome of interest	Understand participants’ perceptions of (1) understanding the problem, (2) assessing prototype feasibility, (3) evaluating the effect of the prototype, and (4) optimizing the design and implementation of the prototype

^a^MedSafeMap: Medication Safety Map.

#### Data Analysis

Observational checklists will be used to code participant behavior recorded on the videos, thereby assessing MedSafeMap’s feasibility and effectiveness. The recordings from the wide-angle video cameras and eye-tracking glasses will be analyzed for themes among participants and across sites by assessing which areas of interest participants fixate on for extended periods. Using gaze duration as a proxy for the wearer’s attention provides insights into which elements of MedSafeMap are influential in shaping pharmacy staff’s behavior. For example, if one of the components of MedSafeMap includes a technician training to speak up when they are concerned that the pharmacist missed a medication-related problem, we can respectively code the reactions of the pharmacist and technician based on the videos [46,47].

Qualitative data from pharmacist and technician stakeholder meetings will be subjected to a rigorous analytic approach [37,48-51]. We will use deductive content analysis, inductive patterns, themes, and categories in our data, guided by our theory-based approach [52]. A conceptual coding structure will be created, and as each interview transcript is added to the analysis, passages will be classified according to existing codes, and codes will be added as needed. Inductive content analysis will also be conducted to determine unanticipated work system characteristics that may facilitate or inhibit resilience.

### Aim 3: Implement and Pilot-Test MedSafeMap

#### Overview

Although simulation-based research can have high internal validity by controlling the highly standardized scenarios that will be developed in aim 2, it is critical to implement and evaluate MedSafeMap in real life, where WAD diverges from WAI, and address external validity concerning pharmacy work systems relevant to CCM. With this approach, we can determine whether changes in performance can be attributed to MedSafeMap rather than other external (eg, regulatory changes) or internal elements (eg, updates to electronic health records) and how such elements can affect MedSafeMap’s performance or impact. The 6 community pharmacies that participated in aim 1 observations and interviews will implement MedSafeMap for optimal interactions designed in aim 2.

#### Implementation and Adaptation

A stepped wedge design [39] will be used, where the MedSafeMap will be sequentially implemented in 2 clusters, each cluster comprising 3 pharmacies (1 pharmacy from each organization; Figure 4). The 2 pharmacies from each organization will be randomized into the 2 clusters. Each cluster will commence with baseline pretest data collection and then cross over from the control condition (before implementation) to the intervention condition, where a formative evaluation of MedSafeMap and the strategies from the implementation guide will be conducted. This evaluation will be performed for each cluster 4 months into its implementation period to consider “what might be missing, what sociotechnical factors had not been considered, and to identify ‘bugs and glitches’ that still need to be addressed” [53]. The evaluation will include one day of observations by shadowing pharmacy staff and may involve short discussions and facilitated reflection from staff at each of the 3 pharmacies in cluster 1. Those observations will be reported to the research team and advisory board to identify opportunities to improve MedSafeMap. Following the formative evaluation in cluster 1, we will refine and improve MedSafeMap and implementation strategies to mitigate vulnerabilities or unintended consequences that may expose patients to new harms or further burden the pharmacists and technicians with more work. The adapted MedSafeMap and implementation strategies will be deployed for cluster 2, which will also undergo a similar evaluation. It is possible that minor adaptations will be made, if necessary, before subjecting the cluster to a posttest evaluation [54] (Figure 4).

**Figure 4 figure4:**

Stepped-wedge design and data collection methods.

#### Evaluation

We will use a sequential explanatory design in which the initial data are quantitative (time and motion study and work volume) and complemented by qualitative data (interviews and medication error reporting). This mixed methods approach will allow the research team to understand variables individually and determine which ones will require further analysis. In line with the CARE and SEIPS 2.0 models, we will collect and analyze data that reflect workflow and care processes and the perspectives of pharmacists and technicians.

#### Time and Motion Study

Our evaluation goal is to examine the impact of MedSafeMap on pharmacists’ and technicians’ ability to be resilient, that is, to successfully attend to unexpected threats while also responding to opportunities [31], such as CCM. To do so, we must understand clinical work processes and the way that care is delivered to patients. We anticipate that MedSafeMap will impact the way pharmacists and technicians perform their work and how they engage each other and their patients. Time and motion studies have been used to measure clinical workflow–related factors, including time and task distributions, frequency of multitasking and interruptions, and who completes tasks, with a goal of improving efficiency [55,56].

We will conduct observations before and after the implementation of the adapted MedSafeMap. Using the observational data collected in aim 1, we will develop a pharmacy work task classification (Table 4). The classifications will be incorporated in the WOMBAT program to allow for the consistent recording of observational data [57,58]. WOMBAT allows observers to time the start and end of tasks and record multiple simultaneous tasks using the multitasking function. If an external factor appears to cause a pharmacist or technician to stop performing one task and start another task, an interruption can be recorded.

**Table 4 table4:** Pharmacy work task classifications.

Work task classification	Examples
What: the task being performed	Counseling and communication with the prescriber
Where: the physical location where the task is undertaken	Behind the desk, in the office, and over the counter
With whom: whom the pharmacy staff was with when performing the task	Alone, patient, technician, and student
How: any tools used to complete the task	Phone, face-to-face, and computer

#### Observer Training

Before MedSafeMap’s implementation and baseline data collection, 2 observers will be trained to use the WOMBAT program. Data collection will begin when simultaneous but independent observations of the same events, such as those seen in Table 4, yield an interrater reliability score of at least 85% [59].

#### Data Collection

Observations will be purposely scheduled across a variety of weekday shifts to maximize data variability and capture the full pharmacy workday. One observer will shadow a pharmacist equipped with a tablet with the WOMBAT software installed on it, while, at the same time, a similarly equipped second observer will shadow a technician. In total, 2 pharmacists and 2 technicians will be observed at each pharmacy. Observations will be limited to three 2-hour sessions per day, each separated by a brief break to reduce participant or observer fatigue. During each break, observers will note down any thoughts regarding future questions or more in-depth observation. The pharmacists and technicians will be observed for 36 hours both before and after implementation, over a 72-hour period. We estimate observing tasks across 72 hours in each pharmacy [55], yielding 432 hours across the 6 participating pharmacies [57,60].

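### One before block and one after block per pharmacy, compared within site with no period term, cannot support attributing change to MedSafeMap rather than to calendar time

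*Protocol article*

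**What the plan says.** All places are in the protocol article, Methods, Aim 3.

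- **Overview:** the approach is said to allow changes in performance to be credited to MedSafeMap, as opposed to external causes (regulatory change is the example) or internal ones (an electronic health record update).
- **Implementation and Adaptation:** a stepped wedge, "sequentially implemented in 2 clusters, each cluster comprising 3 pharmacies". Allocation is random within organization: "The 2 pharmacies from each organization will be randomized into the 2 clusters". On timing: "Each cluster will commence with baseline pretest data collection and then cross over from the control condition". A formative evaluation follows: "This evaluation will be performed for each cluster 4 months into its implementation period". Cluster 2 then receives the version refined after cluster 1's evaluation.
- **Time and Motion Study:** the observations are placed around implementation of the adapted MedSafeMap.
- **Data Collection:** "The pharmacists and technicians will be observed for 36 hours both before and after implementation, over a 72-hour period", "yielding 432 hours across the 6 participating pharmacies". Also: "Observations will be limited to three 2-hour sessions per day".
- **Data Analysis:** for each pharmacy and task category, the share of observed time before is compared with the share after by a z test at 0.05 with Holm adjustment. Neither calendar period nor the other cluster enters.

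**The concern.** A within-pharmacy before-after difference contains everything that changed between the two dates. The examples in the overview, a regulatory change or a record-system update, are calendar-time effects. The stagger between clusters is at least 4 months, because cluster 2 waits for a version that exists only after cluster 1's 4-month evaluation, so such changes could well fall between the blocks.

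A staggered, randomised rollout can provide concurrent controls that remove these effects. Here neither the observation schedule nor the analysis secures that. At stake is whether a shift in time use, for example more time discussing medications with patients, can be credited to MedSafeMap at all.

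**Working it through.** **Inputs.** From the text: 6 pharmacies, 2 clusters of 3, 36 h before and 36 h after per pharmacy, at least 4 months between steps. The drift and variance values below are assumptions; the document gives none.

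**1. The plan's own figure.** 36 + 36 = 72 h per pharmacy; 72 × 6 = 432 h. This reproduces.

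**2. Two blocks per pharmacy.** Let θ be the MedSafeMap effect and c1, c2, c3 the calendar-period effects. The within-pharmacy changes are:

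- Own baseline just before each go-live: cluster 1 gives θ + (c2 − c1); cluster 2 gives θ + (c3 − c2).
- Common baseline: cluster 1 gives θ + (c2 − c1); cluster 2 gives θ + (c3 − c1).

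Each layout offers two equations in three unknowns (θ and two period differences). The rank check agrees. With 6 site effects and 3 period effects, the design has rank 8 without the treatment column and rank 8 with it (9 columns), in both layouts. Three other alignments (common posttest; common pretest and posttest; four separate dates) were also not estimable.

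**3. The exception.** If cluster 2's pretest shares a calendar window with cluster 1's posttest, three live pharmacies face three control pharmacies at the same time. Without fixed site effects, treatment then raises the rank from 3 to 4, so θ is estimable, but with between-pharmacy variation in the error. The common-baseline layout stays non-estimable even so.

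**4. Size of the confounding (assumed drift).** Take a true effect of 0 and a drift of 2 percentage points per step. The planned contrast returns 2 points in both clusters under own baselines, and 2 and 4 points (mean 3) under a common baseline. Over all five alignments the mean bias is 2 to 4 points.

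**5. Three common waves of 24 h.** 3 × 24 = 72 h per pharmacy, 432 h in all. Both clusters are control at wave 1, only cluster 1 is live at wave 2, and both are live at wave 3. Let D be cluster 1's mean minus cluster 2's at a wave. Then D1 = δ, D2 = δ + θ, D3 = δ, and θ is estimated by D2 − (D1 + D3)/2. The rank rises from 8 to 9 of 9 columns, with 18 − 9 = 9 residual degrees of freedom. Under the same drift this estimate returns 0.

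The per-site before-after contrast, if left unchanged, does not. Cluster 1 gives (2 + 4)/2 − 0 = 3 points, and cluster 2 gives 4 − (0 + 2)/2 = 3 points.

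**6. Precision.**

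- Plain before-after contrast, unit variance per 24 h: 36/36 split 2 × 24/36 = 1.333; 24/48 split 1 + 0.5 = 1.5. The ratio is 1.125, and √1.125 = 1.06, so the SE is about 6% larger.
- Time-adjusted estimate, sampling variance 1/hours: (1 + 1/2) × 2 × (1/24)/3 = 0.0417. Uncontrolled pooled contrast: 2 × (1/36)/6 = 0.0093. The ratio is 4.5, so the SE ratio is 2.12.
- If site-by-period variance dominates, the variance ratio tends to 3 and the SE ratio to about 1.7.
- Randomisation: 2³ = 8 allocations, so the smallest two-sided randomisation p is 2/8 = 0.25.

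**7. Version in use at the middle wave.** Suppose the effect is 5 points for the unadapted version and 10 for the adapted one, with cluster 1 unadapted at wave 2. The three-wave estimate is then 5 − (10 − 10)/2 = 5 if cluster 1 later switches, or 5 − (5 − 10)/2 = 7.5 if it does not.

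**The case against.** A reader might infer that observing each pharmacy twice makes the effect inseparable from time under any analysis. The documents do not support that. Non-estimability was shown for site plus categorical period effects. The 3 v 3 concurrent comparison in step 3 is legitimate randomised information if the blocks are aligned. Figure 4, which may show the alignment, was not available for this review. In some alignments an assumed linear time trend would also identify the effect, although a regulatory change or record-system update is not a linear trend. What stands is that the text fixes no alignment and the stated analysis does not use the other cluster.

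A reader might also infer that each block is a single 3-day snapshot. That assumes both observers' hours are summed (2 × 6 = 12 a day, 36/12 = 3 days). If 36 means clock hours it is 36/6 = 6 days, and the section plans to vary the weekday shifts observed. The 72-hour phrase most likely means total observed hours, so it needs clarifying but is not a design fault.

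Nor does the text say that the stepped wedge was chosen to separate MedSafeMap from other changes. The attribution statement comes before the design is introduced, and the staggering also lets the tool be refined between clusters. The statement still describes the aim 3 evaluation as a whole.

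Finally, this is a pilot, the article is condensed, and an analysis plan may exist. But the schedule and the comparison are stated here, and no later plan can recover within-pharmacy identification from waves that were never observed.

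**Conclusion.** The point holds for the time-and-motion data. As written, within-pharmacy change mixes the MedSafeMap effect with calendar change, the planned tests cannot separate them, and the attribution statement is not supported. The rank result needs no numerical assumption beyond site and categorical period effects. The 2 to 4 point bias is only an illustration of an assumed 2-point drift per step.

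Three common waves make the effect estimable at unchanged hours, but only together with a changed analysis. Even then, 6 pharmacies give an estimate with a wide interval rather than a 0.05 test. The point does not extend to the medication-related problem counts, which cover 6 months before and 12 months after. It is worth settling before aim 3 baseline observation starts.

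**What to change.** 1. **Schedule.** Keep 72 hours per pharmacy, but observe all 6 pharmacies in three common calendar waves of 24 hours: both clusters before; cluster 1 live with cluster 2 still control; both live. Match weekdays and times of day across waves. Put this timetable in place of the 72-hour wording.
2. **Version.** State which MedSafeMap version cluster 1 is using at waves 2 and 3, and date wave 2 accordingly.
3. **Analysis.** Add a pooled site-plus-wave (difference-in-differences) estimate with an interval as the attribution analysis. Label the per-site before-after comparisons descriptive.

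**If two blocks are kept:** align cluster 2's pretest with cluster 1's posttest and analyse that 3 v 3 contrast, or withdraw the attribution claim for the time-and-motion data. Against the three-wave fixed-effects estimate, the variance of the aligned two-block analysis ranges from 0.44 to 4.9 times. This is for assumed between-pharmacy variances from about 0 to 10 times the 36-hour sampling variance, with no site-by-period variance.

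**Cost.** Observer-hours are unchanged. There is one more visit block per pharmacy, and cluster 1's baseline and cluster 2's live period each fall from 36 to 24 hours. The plain before-after SE rises by about 6%. The cost that matters is the time-adjusted SE, about 2.1 times the uncontrolled one, or about 1.7 times if site-by-period variance dominates.
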